## 8. STUDY INTERVENTION

### 8.1 Identity of Investigational Products (treatment / medical device)

#### 8.1.1 Experimental Intervention (treatment / medical device)

DREAMS is a mobile application for PwMS and a central data processing unit in a secure computer environment, and a platform that supports study administration.

DREAMS R1.4 is designed and developed to support the feasibility study. During the feasibility study, the study team will evaluate a wide range of digital BioMarker (dBM) candidates as well as technical stability of the device. During the prospective, non-randomized validation study to follow the feasibility study, the study team will evaluate a selection of the most promising digital BioMarker candidates during a cross-sectional and longitudinal study.

Graph 3:

[figure not shown]

Graph 3: DREAMS App

During the study, users are requested to perform a series of tasks (“challenges”). During the challenges, the smartphone’s sensors will gather data that can be analysed to measure the participants’ performance and provide an indication of the level of impairment. Table 6 below summarises each of the challenges and the objectives for these challenges. The cognitive games are provided by PEAK (peak.net) a cognitive game App developer.

Table 6

| # | Challenge Name | Short description                                                               | Objective(s)                                                                     |
|---|----------------|---------------------------------------------------------------------------------|----------------------------------------------------------------------------------|
| 1 | La Promenade   | Walk briskly for 2-minutes, without break                                       | Measure speed, gait and balance                                                  |
| 2 | Musical chairs | Stand-up and sit-down on a chair for 30 seconds                                 | Measure number of completed movements and balance                                |
| 3 | The Butler     | Keep arm up for 10 seconds each, first with eyes open and then with eyes closed | Measure how well user can keep arms up as well as postural tremor in upper limbs |

| #  | Challenge Name                | Short description                                                                                                                  | Objective(s)                                                                               |
|----|-------------------------------|------------------------------------------------------------------------------------------------------------------------------------|--------------------------------------------------------------------------------------------|
| 4  | Penguin                       | Stand with arms along the body for 10 seconds, first with eyes open, then with eyes closed                                         | Measure balance impairment                                                                 |
| 5  | Spanische Treppe              | Walk up and down a set of stairs, answer a few questions regarding the exercise                                                    | Measure functional strength, balance and agility                                           |
| 6  | Schweizergarde                | Make a U-turn after each 5 steps taken                                                                                             | Measure the time it takes to make 5 turns, as well as gait and balance                     |
| 7  | Catch-A-Cloud                 | Touch the moving cloud with index finger as often as possible.                                                                     | Measure the number of touches and the level of accuracy for each attempt                   |
| 8  | Konfetti                      | Keep phone in arm and bend such that the tip of the nose touches the bulls eye on the screen, with both arms, eyes open and closed | Measure how frequent and accurate the user touches the screen, as well as intention tremor |
| 9  | PEAK - Flame Dodge left hand  | Move a character through a series of numbers, while avoiding flames – with the left hand                                           | Measure hand-eye coordination                                                              |
| 10 | PEAK - Flame Dodge right hand | Move a character through a series of numbers, while avoiding flames – with the right hand                                          | Measure hand-eye coordination                                                              |
| 11 | mSDMT (oral)                  | Call out the correct number for the presented symbols using a key.                                                                 | Measure processing-speed of information                                                    |
| 12 | PEAK - Word Hunt              | Find words in a diagram                                                                                                            | Measure language skills                                                                    |
| 13 | PEAK - Spin Cycle             | Observe and recognise changing patterns                                                                                            | Measure working-memory                                                                     |
| 14 | PEAK - Zap Gap                | Sort falling orbs by colour                                                                                                        | Measure mental agility                                                                     |
| 15 | PEAK - Face Switch            | Correctly answer questions about presented faces                                                                                   | Measure mental agility and Inhibition                                                      |
| 16 | PEAK - Rush Back              | Memorize and recall symbols on cards                                                                                               | Measure focus                                                                              |
| 17 | PEAK - Baggage Claim          | Memorize cities and recall them after an distractor challenge is presented                                                         | Measure memory, with distraction                                                           |
| 18 | PEAK - Perilous Path          | Memorise the mines to find a connection between dots without touching the mines                                                    | Measure visuo-spatial memory                                                               |
| 19 | PEAK - Puzzle Blox            | Match a presented shape from a selection of blocks                                                                                 | Measure problem solving                                                                    |

| #  | Challenge Name         | Short description                                                                                        | Objective(s)                                                     |
|----|------------------------|----------------------------------------------------------------------------------------------------------|------------------------------------------------------------------|
| 20 | PEAK - Must Sort       | Sort items by clicking left of right                                                                     | Measure focus                                                    |
| 21 | PEAK - Low Pop         | Tap tiles with random numbers from lowest to highest                                                     | Measure prioritizing and speed                                   |
| 22 | Adlerauge              | Acuity vision test, for both eyes                                                                        | Measure (near) acuity vision (40 cm)                             |
| 23 | Nebel                  | Contrast vision test, for both eyes                                                                      | Measure contrast vision (40 cm)                                  |
| 24 | MSIS-29                | Multiple Sclerosis Impact Scale, see Appendix 17.5.1.1.                                                  | Validated questionnaire (DE version)                             |
| 25 | MSWS-12                | Multiple Sclerosis Walking Scale, see Appendix 17.5.1.2.                                                 | Validated questionnaire (DE version)                             |
| 26 | Fatigue Severity Scale | Fatigue Severity Scale, see Appendix 17.5.1.3.                                                           | Validated questionnaire (DE version)                             |
| 27 | MS Symptom Tracker     | Questionnaire regarding symptoms PwMS has experienced in the last 2 weeks, see Appendix 17.5.1.4.        | Identification of experienced symptoms. Developed by study team. |
| 28 | Feedback Questionnaire | Questionnaire with regards to the acceptance and relevance of the challenges presented in the mobile app | User feedback. Developed by study team.                          |

*Table 6: Description of Challenges*

### 8.1.2 Control Intervention (standard/routine/comparator treatment / medical device)

There is no control intervention.

### 8.1.3 Packaging, Labelling and Supply (re-supply)

DREAMS is a Software as a candidate Medical Device (SaMD) solution. The solution is provided to the study participant via a mobile application (App) on the participant's smartphone, which will be made available via the app stores for Apple (App Store) and Android (Google Play). The study nurse will support the study participant in downloading and setting up the required user account and schedule. Once the App is set up, no further maintenance is required by the study participant.

The App is designed for intended use by lay persons and has examples and instructions that guide the users through each of the functions and challenges. In case the study participant has questions regarding the use of the App or any of the activities, the study

nurse is available for first line support and the manufacturer's support team is available for technical support.

Information about the App, manufacturer and version are included in the "about DREAMS" function in the App. This version of the App is developed for this study, the App is not available to the wider public yet and is not yet registered as a Medical Device.

#### **8.1.4 Storage Conditions**

Not applicable.

### **8.2 Administration of experimental and control interventions**

#### **8.2.1 Experimental Intervention**

Every participant will upload the same version of the DREAMS App (see sections 3.2.5. and 8.1.1) and will perform the same test schedule (see section 3.5.1. Table 5). Every participant will be instructed by the study nurse (App guidance and challenge instructions).

#### **8.2.2 Control Intervention**

There is no control intervention planned.

### **8.3 Dose / Device modifications**

Not applicable

### **8.4 Compliance with study intervention**

Study nurse will be alerted if user completes < 75% of exercises (i.e. missing >2) for at least 2 out of 5 days. The study nurse will contact participants by phone if this is the case to offer help. Participants can contact the study nurse and the study physician anytime. Non-compliance (sustained non-adherence to completion of the scheduled exercises) will result in withdrawal. After withdrawal we will try to get withdrawn participants feedback (semi-structured interview) for understanding the reason for non-compliance.

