## 7.4 Criteria for withdrawal / discontinuation of participants

Patients and healthy controls will be withdrawn from the study if the following occurs during the study period:

- Other clinically significant concomitant disease states (e.g., renal failure, severe hepatic dysfunction, severe/unstable cardiovascular disease, progressive cancer, etc.)
- Non-compliance
- Inability to follow the procedures of the study, e.g. due to language problems, psychological disorders, dementia, etc. of the participant
- Pregnancy: If a participant will realise pregnancy during the study period, she should contact the study nurse. The participant will be allowed to continue the study if she wants to but of course can also withdraw consent immediately.
- Loss of their DREAMS App compatible smartphone (iOS/Android, see section 3.2.4, Table 2)
- Close visual acuity loss of  $< 0.5$
- Loss of hand motor skills not sufficient for using a smartphone
- Using PEAK\* during the study period

\* PEAK: freely available App for cognitive training

Withdrawn participants (drop-out) will be replaced by an additional participant.  
Data of withdrawn participants collected until withdrawal will not be deleted and will be used in a coded form for research purposes.

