#### **11.4 Planned Analyses**

##### **11.4.1 Datasets to be analysed, analysis populations**

All subjects who completed the study will be included in the primary analysis (per protocol analysis). An additional "intention-to-test" analysis comprising all eligible subjects will be performed as a sensitivity analysis.

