### 11.4.2 Primary Analysis

The active tests will be selected using a stepwise selection strategy:

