**A mean response of > 3 on a Likert Scale will be the minimal requirement for test selection.**

b) Adherence will be calculated as percentage of completed repetitions divided by the total number of scheduled repetitions for each test. **The minimal adherence required for test selection will be 80%.**

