### **11.5 Handling of missing data and drop-outs**

Drop-outs will be replaced. Missing data will be handled by multiple imputation. A complete case analysis will be added as a sensitivity analysis.

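### The 80% adherence requirement is judged on completers only, after participants with sustained non-adherence have been withdrawn and replaced, so adherence is biased upward when people give up the App broadly

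*Protocol*

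**What the plan says.** Five provisions of the protocol bear on this point.

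- **The requirement.** Section 11.4.2 opens with "The active tests will be selected using a stepwise selection strategy". In Step 2 b), "Adherence will be calculated as percentage of completed repetitions divided by the total number of scheduled repetitions for each test", and then "The minimal adherence required for test selection will be 80"%. Step 3 ranks only tests that meet this minimum. Step 2 b) does not name the participants who are counted.
- **The analysis set.** Section 11.4.1: "All subjects who completed the study will be included in the primary analysis (per protocol analysis"). The synopsis says the same. An intention-to-test analysis of all eligible subjects is added as a sensitivity analysis.
- **Withdrawal.** Section 8.4: "Non-compliance (sustained non-adherence to completion of the scheduled exercises) will result in withdrawal". Section 7.4 also lists non-compliance as a withdrawal criterion. The word sustained has no numeric definition. The only figure nearby is the alert, "Study nurse will be alerted if user completes < 75% of exercises (i.e. missing >2) for at least 2 out of 5 days", which leads to a phone call and not to withdrawal.
- **Replacement.** Section 7.4: "Withdrawn participants (drop-out) will be replaced by an additional participant". Section 11.5: "Drop-outs will be replaced". Section 11.5 also plans multiple imputation of missing data.
- **Withdrawn participants' data.** Sections 8.6 and 9.2.5 say that these data enter the analysis, under the label of intention to treat. Section 7.4 says that they are kept and used.

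**The concern.** Adherence is a minimum requirement for a test to go forward to the validation study. Under 8.4, low adherence is also a reason to leave the study, and under 11.4.1 those who leave are not in the set on which the requirement is judged. The quantity being estimated helps to decide who is in its own denominator. Someone withdrawn for non-compliance will, over the planned schedule, have adhered less than the average completer. Leaving such people out can therefore only raise the estimate.

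Replacement keeps the number of completers at target, so the completers-only figure stays the same however many people left for non-adherence. What is at stake is the meaning of a pass: it would describe use among people who kept going, whereas the feasibility question is whether people who start will keep going.

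The protocol also contradicts itself on the analysis set. An analyst following 8.6 and 9.2.5 would include the withdrawn participants, while one following 11.4.1 would not. The same test could pass under one reading and fail under the other.

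**Working it through.** **No stated figure to reproduce.** The protocol gives no adherence estimate, drop-out rate or sample-size calculation (11.2). The rates below are assumptions that show how the requirement behaves.

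**Schedule.** Adding up Table 5 (section 3.5.1) gives 7, 7, 11, 7 and 11 challenges on days 1 to 5, so 43 per week and 215 in five weeks. Of the 23 active tests, 20 have 10 planned repetitions. mSDMT, Adlerauge and Nebel are scheduled once a week and have 5.

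**Effect of leaving out the withdrawn.** Take 30 completers (one group, section 6.1) with mean adherence *a*, and *w* withdrawn participants who completed a fraction *b* of the full five-week schedule.

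- Completers only: adherence = *a*, whatever *w* is.
- All who started: (30*a* + *wb*) / (30 + *w*).
- Break-even at 80%: *w* = 30(*a* − 0.80) / (0.80 − *b*).

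With *b* = 0.30 (assumed):

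| Completers *a* | Break-even *w* | Smallest *w* that fails | All-starter adherence at that *w* |
|---|---|---|---|
| 83% | 0.9/0.5 = 1.8 | 2 | (24.9 + 0.6)/32 = 79.7% |
| 86% | 1.8/0.5 = 3.6 | 4 | (25.8 + 1.2)/34 = 79.4% |
| 90% | 3.0/0.5 = 6.0 | 7 | (27.0 + 2.1)/37 = 78.6% |

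At 90%, 6 withdrawals give (27.0 + 1.8)/36 = 80.0%, which still meets a minimum of 80%.

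As a share of all who started, the break-even is (*a* − 0.80)/(*a* − *b*). It runs from 0.05/0.65 = 7.7% (*a* = 85%, *b* = 20%) to 0.15/0.45 = 33.3% (*a* = 95%, *b* = 50%).

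**Effect of the denominator.** Assume 30 completers averaging 8.6 of 10 repetitions, and 6 participants withdrawn after week 2 with 2 of 4 scheduled repetitions done.

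- Scheduled repetitions counted up to withdrawal: (258 + 12)/(300 + 24) = 270/324 = 83.3%.
- Full planned schedule: 270/360 = 75.0%.

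Including the withdrawn is therefore not enough unless the denominator is fixed as well.

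**What is not filtered out.** The alert in 8.4 counts all of a day's exercises together. A participant who drops one test and does the rest completes at worst 6/7 = 85.7% on a day and never triggers it. Such a person would normally remain a completer, and the skipped sessions count against that test: if 7 of 30 completers do none of it, adherence is at most 23/30 = 76.7%, a fail. The upward bias comes from people who give up across the App.

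**The case against.** The best defence has four parts.

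**The protocol already includes withdrawn participants.** Sections 8.6 and 9.2.5 say so. This stands to the extent that exclusion is not settled throughout the document. It does not remove the problem, because 11.4.1 is the section that defines the primary set, and it names completers.

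**The intention-to-test analysis would show any difference.** It may. The phrase about the total number of scheduled repetitions can well be read as the full schedule, so one cannot say that this analysis must fail. But it is a sensitivity analysis, and nothing lets it decide which tests are selected.

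**Completers are a sensible set for reliability.** That is right for the ICC and CV, which need repeated measurements. It does not carry over to adherence, where stopping is part of the outcome.

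**Not every withdrawal reflects adherence.** Section 7.4 also covers concomitant disease, loss of the smartphone and loss of vision or hand function. Counting all sessions after such events as refusals would bias adherence downward. This stands, and the fix allows for it.

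A reader might also infer two stronger claims. The first is that any test participants abandon can pass. The schedule arithmetic does not support this for one test skipped by otherwise compliant completers. The second is that replacement conceals the drop-out rate. Nothing in the protocol prevents withdrawals from being counted and reported: 7.4 keeps the data, and 8.4 seeks the reasons for non-compliance.

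**Conclusion.** The concern holds in a limited form. Followed as written, 11.4.1 and 11.4.2 judge the 80% requirement on people from whom sustained non-adherers have been removed by rule and replaced. For broad non-adherence the bias is upward and affects tests across the board; test-specific skipping by completers is still captured. Sections 8.6 and 9.2.5 cannot be squared with 11.4.1 as the text stands.

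The direction is clear from the rules. The size is not, because the protocol gives no rates. If withdrawn participants did 30% of the full schedule, 2, 4 or 7 withdrawals per 30 completers reverse a pass at completer adherence of 83%, 86% or 90%. With few withdrawals, or completers well above 80%, the decision would not change. A reader should not infer that selection will be wrong, only that the requirement cannot show broad abandonment.

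This should be fixed, but it is not fatal. Adherence is a selection requirement and is not among the three primary outcomes in 5.1, and selected tests go on to a separate validation study.

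**What to change.** 1. Reconcile 11.4.1 with 8.6 and 9.2.5, so that the protocol says once which participants enter which analysis.
2. In 11.4.2 Step 2 b), apply the 80% requirement to all enrolled participants who started the App, including those later withdrawn and replaced.
3. Use each test's planned five-week repetitions from Table 5 as the denominator (10 for most tests, 5 for the three weekly ones). Where a participant is withdrawn for non-compliance or leaves by choice, count missed sessions before and after withdrawal as not completed. State that the multiple imputation in 11.5 does not apply to them.
4. For withdrawals unrelated to adherence, such as loss of the smartphone or concomitant disease, count scheduled sessions up to withdrawal, with the full-schedule count as a sensitivity analysis.
5. Show completers-only adherence as a sensitivity analysis, and report the number withdrawn and replaced by reason.

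Completers and replacement may stay for the ICC and CV analyses. With this rule, the missing definition of sustained matters much less to selection, because leaving for non-compliance no longer removes anyone from the denominator.

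The cost is a few sentences in 11.4.1, 11.4.2, 11.5, 8.6 and 9.2.5. Completion is already recorded by the App (3.5.1, 12.2.1), so no new data are needed. The downside is that adherence figures become less favourable.

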### **8.5 Technical Support**

There will be a technical support from our main development partner Healios GmbH for the clinical team (study nurse, study physician and all investigators). IT issues will be classified the same day into two main categories: "critical" or "non critical". "Critical" IT issues will be addressed the same day, "non critical" IT issues within two business days. The Healios team is not permitted to contact the participants directly.

## **8.6 Data Collection and Follow-up for withdrawn participants**

Data from withdrawn participants (drop out) will be included into analysis (intention to treat analysis). Withdrawn participants will be asked if they would be willing to be invited for the feedback interview in order to learn from their experience with the App. This will take place in study visit V3. The study design has no official follow-up visit.

